### 2.7. Adverse events

Adverse events (AEs) will be reported and graded according to the revised NCI Common Terminology Criteria for Adverse Events (CTCAE) version 5.0. Investigators must promptly notify the Principal Investigator (PI) of any unanticipated problems or life-threatening complications. Any adverse events occurring after the initial dose of study treatment, during treatment, or within 30 days of the last dose, must be reported to the PI using the local institutional SAE form. All expected and unexpected AEs will be communicated to the PI, who will then report them to the institutional review board. Serious adverse events must be reported within 24 hours of occurrence or discovery. All adverse events, both serious and non-serious, along with any deaths occurring during the study initiation, intervention, and within 30 days of the last study intervention, will be monitored until resolution, stabilization, or until the investigator determines the event to be irreversible, or the participant is lost to follow-up. Adverse events will be documented in the participant’s medical records and the appropriate case report forms. Given the remote nature of the exercise sessions, additional safety measures include providing specific exercise and assessment recommendations (e.g., standing near a wall for balance activities), adapting exercise protocols as needed (e.g., limiting weight or modifying resistance exercises), verifying participants’ home addresses to enable emergency response, and ensuring up-to-date emergency contact information is available for all participants.

### 2.8. Data management plan and timeline of study

Participant recruitment started in September 2022. Currently 18 patients consented, and 19 patients have completed the intervention. Data is monitored internally within DFCI for timeliness of submission, completeness, and adherence to protocol requirements. Monitoring begins at the time of patient registration and continues throughout protocol performance and completion. The study team collects, manages, and performs quality checks on the data. Potential audits or inspections may be conducted by the principal investigator or their designated representatives. All data is stored on a secure network drive using REDCap, a HIPAA-compliant web-based application hosted by Partners HealthCare Research Computing, Enterprise Research Infrastructure & Services, on password-protected computers. Any hardcopy data is stored in locked filing cabinets in card-access facilities.

### 2.9. Sample size calculation

We plan to recruit 45 patients (n = 15 per group). This sample size was determined based on recommendations of samples sizes between 24 and 50 for feasibility studies for assessing the feasibility of the intervention and estimating effect sizes for designing future studies. [61–63] The primary endpoint of this study is feasibility of the resistance exercise combined with protein supplementation intervention. When the sample size n = 15 in the resistance exercise combined with protein supplementation group and the true feasibility rate of 85%, we can observe a feasibility rate ≥70% with the probability of 82%.

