### 2.10. Statistical analysis

Based on the intention-to-treat principle, the primary analysis population is all randomized subjects. The secondary analysis population is the per-protocol set (analysis that only includes patients’ data for those who were compliant to the study protocol). The primary endpoint of this pilot study is feasibility of resistance exercise combined with protein supplementation (RE + PS). Using the data from the patients assigned to the RE + PS, we will calculate the point estimate and corresponding exact 95% confidence interval (CI) for the feasibility. For the other outcomes (i.e., skeletal muscle outcomes and biomarkers), we will use standard statistical techniques. We will use descriptive statistics to summarize the data. For within-group comparison (i.e., pre- vs. post-intervention comparison), we will use paired t-test or Wilcoxon signed-rank test for continuous outcomes and McNemar’s test for dichotomous outcomes. For pairwise comparisons between two groups, we will use two-sample t-test, Wilcoxon rank sum tests, Fisher’s exact tests, and so on. ANOVA and logistic regression analyses will be used to explore the association of the baseline characteristics with outcome. For longitudinal data, we will use generalized linear mixed effects models.

The primary analysis includes all completed outcome assessments (regardless of whether patients stayed on the intervention), inviting those who drop from the intervention to return for outcome assessments. The only missing data here would be those who drop the intervention and do not return for outcome assessments; this includes patients withdrawn due to noncompliance. Preliminary analyses will compare patients who do and do not contribute to this analysis on baseline characteristics. A sensitivity analysis will include multiple imputation of all missing outcome data, so that this analysis would be a complete case analysis, with data for all outcome time points.

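### Section 2.9 gives 82% as the probability of observing a feasibility rate of at least 70% with 15 patients and a true rate of 85%; the exact figure is 94%

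*Protocol article*

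**What the plan says.** Section 2.9 (Sample size calculation) of the protocol article first bases the total of 45 patients, 15 per group, on published recommendations of 24 to 50 participants for feasibility studies. It names feasibility of resistance exercise plus protein supplementation as the primary endpoint. It then gives one probability statement for that arm. The condition is "When the sample size n = 15 in the resistance exercise combined with protein supplementation group and the true feasibility rate of 85" per cent, and the conclusion is that "we can observe a feasibility rate ≥70% with the probability of 82" per cent.

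Section 2.10 (Statistical analysis) confirms the same primary endpoint. For the RE + PS arm it says "we will calculate the point estimate and corresponding exact 95% confidence interval (CI) for the feasibility", and under intention to treat "the primary analysis population is all randomized subjects". The article gives no other power, error rate or probability for the primary endpoint.

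**The concern.** The sentence in section 2.9 holds everything needed to check it: a sample size, a true rate, a threshold on the observed rate, and the resulting probability. With only 15 patients the observed rate moves in steps of 1/15 (6.7 percentage points), so the threshold corresponds to a definite count and the probability follows from the binomial distribution. The printed figure does not follow.

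This is the only probability-based support for having 15 patients in the primary-endpoint arm. It is also the only place where the article sets 70% against an observed feasibility rate in that arm. If the threshold and the probability imply different counts, a reader cannot be sure that the calculation was run for the threshold in print.

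**Working it through.** **Inputs, all from section 2.9**

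- n = 15 (RE + PS arm)
- true feasibility rate p = 0.85
- threshold: observed rate of at least 0.70
- stated probability: 0.82

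**Step 1: turn the threshold into a count.** 0.70 × 15 = 10.5, so the smallest qualifying count is 11. Check: 11/15 = 73.3% qualifies; 10/15 = 66.7% does not.

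**Step 2: exact binomial tail.** P(X ≥ r) = Σ C(15, k) × 0.85^k × 0.15^(15−k), summed over k = r to 15.

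| Cut-off r | Observed rate at cut-off | P(X ≥ r) |
|---|---|---|
| 10 | 66.7% | 0.9832 |
| 11 | 73.3% | **0.9383** |
| 12 | 80.0% | **0.8227** |
| 13 | 86.7% | 0.6042 |

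The threshold as printed gives 93.8%. The printed 82% sits on the row for 12 of 15. The difference, 0.9383 − 0.8227 = 0.1156, is the probability of exactly 11 feasible patients.

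**Step 3: try to reproduce 82% in other ways.**

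- *Normal approximation.* The standard error is √(0.85 × 0.15 / 15) = 0.0922, so z = 0.15 / 0.0922 = 1.63 and the probability is 0.948. A continuity correction gives 0.897. Using the variance at 0.70 gives 0.898.
- *Other sample sizes at p = 0.85 with the 70% threshold.* For n from 10 to 18 the lowest probability is 0.882 (n = 13, at least 10). None gives 0.82.
- *Both exercise arms pooled.* With n = 30 and at least 21, the probability is 0.990.
- *Another true rate with at least 11 of 15.* A rate of 0.79 gives 0.809 and 0.80 gives 0.836. These bracket 0.82, but the article states 85%.
- *Dropouts counted as failures, on top of 85%.* A 5% loss (true rate 0.85 × 0.95 = 0.8075) gives 0.855; a 10% loss (0.765) gives 0.735. Some loss between the two would give about 0.82, but section 2.9 applies no such allowance.

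Of the variants that keep n = 15 and p = 0.85 as stated, only a cut-off of 12 gives 82%.

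**The case against.** The best case on the other side accepts the arithmetic and disputes its importance. Most of it stands.

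- **The sample size does not rest on this sentence.** Section 2.9 says the size came from the 24 to 50 recommendation, and 45 lies in that range. The probability statement follows as a description of what 15 patients deliver. A reader might infer that the wrong figure leaves the sample size unjustified or too small. It does not: the true probability is higher than the printed one, so the error is conservative.
- **A cut-off of 12 is an inference.** Neither 12 of 15 nor 80% appears in the article. The match is close (82.3%), and a strict inequality or an intended 80% threshold would each explain it, but so might a different true rate or an unstated dropout allowance. The source cannot be settled from the text.
- **No pass/fail rule on a patient count is written down.** A reader might infer that the trial's verdict flips when exactly 11 of 15 patients are feasible. Section 2.10 plans only an estimate with an exact interval, so the article does not support that claim.
- **The 70% elsewhere is a different quantity.** In the Introduction's hypothesis and in section 2.6.1 it is a share of sessions or of protein doses, not of patients. It cannot be used to show that 11 of 15 was the intended patient-level cut-off.
- **The lack of a false-positive rate is no finding here.** The article states no unacceptable feasibility rate, and that detail may sit in the full protocol or analysis plan.

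None of this rescues the printed figure. It is contradicted by its own stated inputs, and neither condensation into an article nor an unseen analysis plan explains that.

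**Conclusion.** The point holds as a numerical error with limited consequences. For n = 15, a true rate of 85% and an observed rate of at least 70%, the probability is 93.8%; the article prints 82%, which is 11.6 points too low after rounding 82.3% down to 82%. The threshold and the probability in that sentence cannot both be right for the stated inputs.

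The calculation assumes independent patients with a common feasibility probability and a denominator of 15. That fits the planned exact interval and the all-randomized analysis population. The planned estimate and confidence interval are unaffected, as is the number of patients. What needs correcting is the one operating characteristic published for the primary endpoint, together with the doubt it leaves about which count the authors had in mind.

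**What to change.** Rewrite the last sentence of section 2.9 in one of two ways, according to what was intended:

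- keep the threshold: with 15 patients and a true rate of 85%, an observed rate of at least 70% (at least 11 of 15) has probability 94%; or
- keep the probability: an observed rate of at least 80% (at least 12 of 15) has probability 82%.

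If the calculation instead used another true rate or a dropout allowance, state that input and recompute. In every case print the integer count beside the percentage. Section 2.8 shows that the trial is under way, so the choice should be made and dated before the primary data are analysed; otherwise a result of 11 of 15 would invite a choice made after the fact. The cost is one sentence, with no extra patients and no change to conduct or to the planned analysis.

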### 2.10. Statistical analysis

Based on the intention-to-treat principle, the primary analysis population is all randomized subjects. The secondary analysis population is the per-protocol set (analysis that only includes patients’ data for those who were compliant to the study protocol). The primary endpoint of this pilot study is feasibility of resistance exercise combined with protein supplementation (RE + PS). Using the data from the patients assigned to the RE + PS, we will calculate the point estimate and corresponding exact 95% confidence interval (CI) for the feasibility. For the other outcomes (i.e., skeletal muscle outcomes and biomarkers), we will use standard statistical techniques. We will use descriptive statistics to summarize the data. For within-group comparison (i.e., pre- vs. post-intervention comparison), we will use paired t-test or Wilcoxon signed-rank test for continuous outcomes and McNemar’s test for dichotomous outcomes. For pairwise comparisons between two groups, we will use two-sample t-test, Wilcoxon rank sum tests, Fisher’s exact tests, and so on. ANOVA and logistic regression analyses will be used to explore the association of the baseline characteristics with outcome. For longitudinal data, we will use generalized linear mixed effects models.

The primary analysis includes all completed outcome assessments (regardless of whether patients stayed on the intervention), inviting those who drop from the intervention to return for outcome assessments. The only missing data here would be those who drop the intervention and do not return for outcome assessments; this includes patients withdrawn due to noncompliance. Preliminary analyses will compare patients who do and do not contribute to this analysis on baseline characteristics. A sensitivity analysis will include multiple imputation of all missing outcome data, so that this analysis would be a complete case analysis, with data for all outcome time points.

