Thus, the ongoing REBUILD trial is a three-armed pilot randomized controlled trial designed to evaluate the feasibility of a home-based virtually supervised resistance exercise intervention, with or without protein supplementation, in pancreatic cancer patients initiating neoadjuvant chemotherapy. Our secondary aim is to examine the effects of home-based virtually supervised resistance exercise combined with or without protein supplementation on skeletal muscle mass, plasma biomarkers associated with muscle tissue wasting, physical function and psychosocial measures. We hypothesize that a home-based virtually supervised resistance exercise intervention with or without protein supplementation will be feasible, with at least 70% of exercise sessions completed and protein supplementation consumed among pancreatic cancer patients undergoing neoadjuvant chemotherapy. Furthermore, we hypothesize that a home-based virtually supervised resistance exercise combined with protein supplementation will elicit greater maintenance of skeletal muscle mass and improvements in plasma biomarkers associated with muscle wasting compared with resistance exercise alone and attention controls. Lastly, we hypothesize that resistance exercise alone or in combination with protein supplementation will improve physical function and psychosocial measures when compared to attention controls.

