### 2.4. Randomization and blinding

Upon completion of baseline testing, patients are randomly assigned to either RE, RE + PS or AC groups in an equal allocation ratio (1:1:1) using a permitted block design with varying block size. The study biostatistician ([name]) prepared the randomization schema prior to trial start-up, and the randomization allocation was provided to staff via a web-based application (REDCap). Study investigators are blinded to the randomization process. The intervention allocation is not blinded to the study patients, interventionists, and outcome assessors due to the nature of exercise intervention.

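### No baseline-adjusted arm difference is specified for the continuous secondary and tertiary outcomes; the unadjusted two-sample tests named are valid but less precise than the collected baselines would allow at 15 per arm

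*Protocol article*

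**What the plan says.** Section 2.10 gives each family of methods a task.

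- Between arms: "For pairwise comparisons between two groups, we will use two-sample t-test, Wilcoxon rank sum tests", followed by Fisher's exact test and an open-ended remainder. It does not say whether these are applied to follow-up values or to changes.
- Within arms: "For within-group comparison (i.e., pre- vs. post-intervention comparison), we will use paired t-test or Wilcoxon signed-rank test for continuous outcomes".
- Regression: "ANOVA and logistic regression analyses will be used to explore the association of the baseline characteristics with outcome". This concerns predictors of outcome; no adjusted arm effect is mentioned.
- Mixed models: the paragraph ends by assigning generalized linear mixed models to longitudinal data. It names no outcomes, no fixed effects and no treatment of the baseline value, and does not say whether this model or the two-sample tests carry the between-arm result.

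Section 2.6 puts baseline testing before randomization and has one further testing point after the intervention. The Introduction's hypothesis on muscle and biomarkers is between-arm: RE + PS "will elicit greater maintenance of skeletal muscle mass and improvements in plasma biomarkers associated with muscle wasting compared with resistance exercise alone and attention controls". Physical function and psychosocial measures are likewise hypothesized against attention control. Section 2.9 gives effect-size estimation for later trials as one purpose of the sample.

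**The concern.** The hypotheses and the effect sizes for a later trial both need a between-arm estimate, and arms of 15 leave little precision to spare. A baseline measured before randomization is the cheapest source of more, and the plan does not commit to using it.

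If the two-sample tests are run on follow-up values, all the between-patient variation that baseline explains stays in the error term. Skeletal muscle index is the clearest case. Section 2.6.2 uses sarcopenia cut-offs of 38.5 cm²/m² for women and 52.4 for men, and section 2.4 names no stratification factor, so a chance sex imbalance would move an unadjusted follow-up difference.

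The within-arm tests sit beside the between-arm tests with no statement of their role. They cannot show that one arm did better than another.

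**Working it through.** The article gives no standard deviation, correlation, power or detectable difference for these outcomes, so there is no figure of its own to reproduce.

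**Inputs from the article.** "We plan to recruit 45 patients (n = 15 per group"), allocated "in an equal allocation ratio (1:1:1"); one baseline and one follow-up value.

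**Assumptions.** Equal SD (σ) at both visits and in all arms; common pre-post correlation r, shown over a range; complete data; two-sided 5% level; two arms compared at a time.

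**Variance of the arm difference, n per arm.**
- Follow-up values: 2σ²/n
- Change scores: (2σ²/n) × 2(1 − r)
- ANCOVA: (2σ²/n) × (1 − r²), times a small-sample penalty 1 + 1/(2n − 4) = 1 + 1/26 = 1.038 at n = 15

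The large-sample ratio for ANCOVA is therefore 1 − r² against follow-up values and (1 − r²)/[2(1 − r)] = (1 + r)/2 against changes. Effective n is 15 divided by the penalized ratio.

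| r | vs follow-up: ratio | penalized | effective n | vs change: ratio | penalized | effective n |
|---|---|---|---|---|---|---|
| 0.5 | 0.75 | 0.779 | 19.3 | 0.75 | 0.779 | 19.3 |
| 0.7 | 0.51 | 0.530 | 28.3 | 0.85 | 0.883 | 17.0 |
| 0.9 | 0.19 | 0.197 | 76.0 | 0.95 | 0.987 | 15.2 |

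**In units of σ**, from the t distribution (28 degrees of freedom for the t-tests, 27 for ANCOVA). Power is for an assumed true difference of 0.8 SD. Order: follow-up / change / ANCOVA.

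| r | 95% CI half-width | power |
|---|---|---|
| 0.3 | 0.75 / 0.89 / 0.73 | 43% for change, 56% for follow-up, 58% for ANCOVA |
| 0.5 | 0.75 / 0.75 / 0.66 | 56% / 56% / 67% |
| 0.7 | 0.75 / 0.58 / 0.55 | 56% / 78% / 83% |
| 0.9 | 0.75 / 0.33 / 0.33 | 56% / 99.7% / 99.7% |

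A simulation of 5,000 trials at each of r = 0.5, 0.7 and 0.9 agreed (at r = 0.7: 57%, 78%, 83%). At r = 0 adjustment costs almost nothing: half-width 0.76 against 0.75.

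**Sex and muscle index, follow-up values only.** For illustration, suppose half the patients are men and the cut-off gap, 52.4 − 38.5 = 13.9 cm²/m², stands in for the sex difference in means. The difference in proportion male between two arms of 15 has standard error √(2 × 0.25/15) = 0.183, so sex alone contributes 13.9 × 0.183 ≈ 2.5 cm²/m² to the standard error of the arm difference.

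**Within-arm tests.** Give two arms the same true change of 0.3 SD with r = 0.7. The SD of change is √(2 × 0.3) = 0.775, the noncentrality is (0.3/0.775) × √15 = 1.5, and each paired t-test has power 0.287. Exactly one of the two arms is significant with probability 2 × 0.287 × 0.713 = 0.41.

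**The case against.** The list of tests is open-ended, and data from two visits could fall under the mixed-model sentence. A reader might infer that the plan has chosen unadjusted tests in place of an analysis that uses baseline. The text does not support that: the mixed model may cover these outcomes, and how baseline enters it is simply not stated. But the sentence does not settle the matter either. With complete data and one follow-up value, a model with free arm-by-visit means reproduces the change-score contrast; only one that holds the baseline mean common to all arms gains what ANCOVA gains. Neither form is designated.

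A reader might also infer that about half the information is thrown away, or that sex imbalance will drive the muscle results. Both follow only if the tests use follow-up values, which the article never says. Its hypotheses are worded as maintenance and improvement, so change scores are at least as natural a reading. Changes remove a stable level difference between men and women, and different cut-offs do not imply different expected change.

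Nor does the article say that within-arm p-values will be used to support the between-arm hypotheses; it lists separate between-arm tests. The 41% figure is a reason to label the paired tests, not evidence of a planned misuse.

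Finally, a condensed article may leave model detail to the full protocol. That covers the mixed model's specification. It does not cover the between-arm method that the article itself names and that can be improved.

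**Conclusion.** The point stands as one about efficiency. Unadjusted comparisons of randomized arms are valid, so this is not the correction of an error. The stated between-arm method can nevertheless be improved at almost no cost, and the analysis that carries the between-arm estimate should be identified.

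The gain rests on two unstated inputs. Against follow-up values it is substantial over the range of r shown. Against change scores it is moderate at r = 0.5, small at r = 0.7 and close to nil near 0.9. Whichever the authors meant, ANCOVA is never materially worse, and it removes the need to choose. What is affected is the precision of the secondary and tertiary effect sizes to be carried into a later trial. The primary endpoint, feasibility in the RE + PS arm with an exact interval, is untouched.

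**What to change.** In section 2.10, state that for each continuous secondary and tertiary outcome the between-arm estimate comes from an ANCOVA of the follow-up value on arm and the baseline value of the same outcome, or from a mixed model on both visits with a common baseline mean. Analyze skewed biomarkers on the log scale. Report the pairwise adjusted differences with 95% confidence intervals (as ratios after back-transformation for logged outcomes). For skeletal muscle index, consider adding sex as a covariate. Label the within-arm pre/post tests as descriptive.

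The cost is analysis wording and one degree of freedom, or two where sex is added. Data collection, sample size and the primary analysis do not change.
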